### 3.3. Assignment of Interventions

In order to create a nationally representative sample, the public information available on the websites of all County School Inspectorates (41 counties plus the Romanian Capital) was analyzed. This process involved the evaluation of publicly available information from 4696 schools, which aided the understanding of the territorial distribution of the target population.

The national representative sample is stratified and randomized. The stratification was performed at the level of administrative units (counties), and on locality type (i.e., urban versus rural localities). For each county, the total number of pupils and the percentage of children for each of these administrative units were computed. The percentage was used to estimate how many children would have to be included in each county. The number was then divided based on locality type (i.e., urban versus rural), and the final target number of evaluations was obtained. The MS Excel’s randomization function was used for each county to select an urban and a rural nursery.

The steps of the allocation sequence are as follows:The order of the counties is decided—each collection point receives several counties and the research team can decide in which county it would be more convenient.Kindergartens in the respective county are contacted to determine their availability to participate in the study and the number of children from the target population available for evaluation.If the 2 kindergartens that are contacted together have at least 18 children (out of the required 25), data collection can begin in the respective county.

If the 2 kindergartens contacted do not have at least 18 children together, the next county on the list will be selected and the procedure returns to steps 2 and 3.

E-mails will be sent to the correspondence address provided to generate the allocation sequence. Consent in principle and an estimate of the number of children in the target population will be requested. If there is no response within the next 5 working days, the kindergarten will be called in to check that the e-mail was received in good condition (e.g., to obtain a working e-mail address or to see the status of the request).

Once the study has been accepted, the director of the nursery will be contacted by telephone to arrange details of the timing of the evaluation, to select the date on which the evaluation will take place, and to find out (by telephone) the number of classes. Consent forms and questionnaires will be sent by courier at least 7 days before the assessment date and their receipt and distribution to parents checked by phone 3 days after sending by courier. The return rate of the questionnaires will be checked by telephone (how many questionnaires have been returned, how many consent forms have been signed by parents) 2 days before the assessment date.

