## 2. Experimental Design

The study is designed and planned as an RCT, taking into consideration the early diagnosis of caries lesions through clinical examinations in the nurseries, control of risk factors through the evaluation of oral health-related knowledge, and behaviors, health education, and evaluation of the efficacy to arrest caries’ progression through the application of fluoride toothpaste. The trial will also develop new primary care teams—dental hygienists. This will provide a framework for integrating the prevention and control of dental caries into general health interventions.

In accordance with the informed consent, all personal data of the participants will be kept anonymous. The participants will receive a unique ID which will be used for data entry on an online software. The ID will be used for each clinical examination and data will be entered accordingly. As stated by Romanian regulations, an archive of the data has to be kept for 5 years after the trial in the secured archive of the university. The program was approved and registered by the Ethical Committee of the “Victor Babes” University of Medicine and Pharmacy Timișoara, Romania, under trial No. 18688/23.10.2023 and Protocol NCT06441500/28.05.2024 released on https://clinicaltrials.gov/, accesed on 29 May 2024, protocol version 1.

The project will be implemented in collaboration with the universities of Medicine and Pharmacy in Bucharest, Timișoara, Cluj-Napoca, Craiova, Iasi, and Targu Mures in order to ensure a homogeneous distribution of the evaluation sites, covering the whole country. The study group will consist of kindergarten children. The pathfinder sampling technique will be used to obtain a representative sample. Selection of nurseries will be performed according to the pathfinder sampling technique. As suggested by the World Health Organization (WHO), this survey’s design is suitable for the collection of data for planning purposes and monitoring of oral health programs in all countries regardless of the level of disease, availability of resources, or complexity of care.

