The number of children is based on an initial calculated requirement of 415 participants, with an additional 10% (rounded up from 456.5 to 460) added to account for potential dropouts or loss to follow-up. The sample is stratified based on administrative units and locality type and randomization is ensured by using the MS Excel function. Children will be included based on the enrolment in kindergarten, consent of the parents, and assent from the child. The exclusion criteria are represented by chronic general diseases or a history of allergic reactions, the presence of fluorosis or other enamel deficiencies, and non-collaborative behavior. The selection can be seen in the flowchart in Figure 1.

The nationally representative sample will be evaluated at baseline using self-assessment tools and clinical examination. During the intervention, evaluations will be performed every 6 months.

The program is designed to deliver additional clinical prevention activities through dental hygienists, aimed at children aged four to six, a special priority being afforded to nursery establishments, in order to improve the oral health of young children and complement the established national toothpaste/toothbrush scheme. The activity flow chart can be seen in the figure below (Figure 2).

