### Study Setting

The total sample size is calculated according to the WHO guidelines using a stratified sampling technique for examination sites in Romanian cities: Bucharest, Timișoara, Cluj-Napoca, Craiova, Iasi, Targu Mures, and the surrounding geographical areas. Data collection points (Figure 3) will be 4 kindergartens in the Capital or metropolitan areas, 2 kindergartens in each of 2 large cities, and 1 kindergarten in each 4 villages from different geographic areas (Dobrogea, Moldova, Ardeal, Muntenia). Metropolitan areas in Romania are Iași, Brașov, Oradea, Târgu Mureș, Cluj Napoca, Craiova, Roman, Baia Mare, Satu Mare, Timișoara and Arad. Romania is divided into 40 counties (regional administrative sites consisting of several cities and villages), the capital, Bucharest being considered on its own. Further on, it is divided into metropolitan areas (over 250,000 inhabitants), large cities (100,000–250,000 inhabitants), small cities (less than 100,000 inhabitants), and villages (less than 5000 inhabitants). A detailed list of the study sites can be obtained from the project manager.

Children aged 4–6 years, enrolled in kindergartens in Romania will be included in the study, providing they show signed informed consent from their parents/caregivers. Parents or caregivers are responsible for signing the consent form for children and any subject may withdraw from the study at any time after recruitment. The examiners shall collect the informed consent forms prior to the examination. Before each examination, each subject will have the free will to participate by direct inquiry.

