### 3.1. Strategies to Improve Adherence to Interventions

Adherence to intervention protocols will be constantly monitored and evaluated. Evaluation of the intervention will focus on three main domains as follows:Specific training for dental hygienists to deliver oral health promotion to children, parents, and nursery staff, focusing on tailoring key messages to the specific age at visit outlined in the care pathway, and on practical preparation for delivering interventions in the nurseries. All the procedures used to assess the outcomes of each activity will be tailored to the specific outcomes. Questionnaires will be developed by a team of sociologists and psychologists, pretested, and used before and after the interventions in order to assess possible changes in knowledge level. The questionnaires will be structured into three distinct sections: the first referring to personal characteristics, the second addressing general knowledge concerning both general and oral health, and the third focusing on awareness related to the dissemination of information and educational competencies. The Capacity-Building Framework will be used to link knowledge to actions that test the skills acquired.A toothpaste/toothbrush scheme involving free daily tooth brushing will be established for each 4- and 6-year-old child attending nursery, along with the free distribution of toothpaste/toothbrush packs to every child on at least 8 occasions (every 3 months). Daily tooth-brushing activities will be monitored by qualitative research, meaning that interviews with the educators will be used to assess the number of children who attend the kindergarten, the number of children who actually perform daily tooth brushing, the use of toothpaste, and any barriers in the implementation of the tooth-brushing scheme. The distribution of necessary materials, correct delivery of products, cost analysis showing price trends and percentage differences over the time span, and consumer price index evaluation for the given time span will be assessed as part of the cost efficiency analysis.Evaluation of clinical outcomes—caries activity levels—after implementing the daily tooth-brushing scheme. The outcomes will offer information regarding the particularities of the clinical investigation for the specific age group and the time necessary for the investigation and intervention.

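### Section 3.3 presents a site-sampling procedure as the allocation sequence; followed as written it assigns no one to intervention or control

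*Protocol article*

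**What the plan says.** Section 2 of the protocol article declares the design: "The study is designed and planned as an RCT". On randomisation it adds: "The sample is stratified based on administrative units and locality type and randomization is ensured by using the MS Excel function".

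Section 3.3, headed Assignment of Interventions, opens in the same way: "The national representative sample is stratified and randomized". It reports that the Excel "randomization function was used for each county to select an urban and a rural nursery". It then lists what it calls the steps of the allocation sequence:

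1. The order of counties is settled: "each collection point receives several counties and the research team can decide in which county it would be more convenient".
2. Kindergartens in that county are contacted about availability and numbers of eligible children.
3. If the two kindergartens contacted have at least 18 children between them, out of 25 required, data collection can start. If not, the next county is taken.

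The section goes on to say that e-mails to kindergartens serve to generate this sequence.

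On who receives the intervention, Section 3 (Procedure) describes free daily brushing for every child of the target ages attending nursery. Section 3.1 adds "free distribution of toothpaste/toothbrush packs to every child on at least 8 occasions".

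Section 3.5 plans comparisons between groups: baseline comparability, a Mann–Whitney test on the number of events, ITT and per-protocol analyses, a risk ratio and an NNT. Section 1.1 states a null hypothesis of no effect on caries status.

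**The concern.** An allocation sequence should end with each unit in an arm. This one ends with a site entering the study. Someone carrying out Section 3.3 to the letter would finish with a list of kindergartens and no intervention or control group.

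This is not a detail that a condensed article leaves to a fuller document. The article does print an allocation procedure, under the heading where a reader looks for it, and what it prints is a different procedure. A statistical analysis plan could not repair it either, because allocation is trial conduct and not analysis.

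At stake is the causal reading of the primary result. If every child receives the scheme, caries change over the 24 months cannot be separated from ageing. If two groups are formed by a route that is not written down, a difference between them cannot be attributed to the intervention by virtue of randomisation.

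**Working it through.** **Side-by-side reading.** The question at each place is whether it puts any unit into an arm.

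| Place in the article | What it does | Assigns an arm? |
|---|---|---|
| Section 2, Excel sentence | Stratifies and randomises the sample | No |
| Section 3.3, Excel sentence | Picks one urban and one rural nursery per county | No |
| Section 3.3, step 1 | Orders counties, with convenience allowed | No |
| Section 3.3, step 2 | Checks availability | No |
| Section 3.3, step 3 | Applies the 18-child threshold, then data collection | No |
| Section 3.3, e-mails | Seeks agreement in principle and child numbers | No |
| Table 1 | Allocation mark at timepoint 0, after screening and consent | Names the step, gives no method |
| Figure 1 | Captioned as the RCT flowchart; not shown | Cannot be read |
| Sections 3 and 3.1 | Give brushing and packs to every child | No comparison group described |
| Section 3.5 | Compares groups | Presupposes arms |

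The visible text names no unit of allocation, no ratio and no control condition.

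**Does the sample size imply two arms?** The stated total follows from its base: 415 × 1.10 = 456.5, which Section 2 rounds up to 460. Section 3.2 gives SD 2, z-values 1.96 and 1.28, and design effect 2, but no numerical effect size. The difference δ therefore has to be assumed, as does a 1:1 ratio. For two equal arms:

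N = design effect × 2 arms × 2 × SD² × (1.96 + 1.28)² / δ² = 2 × 2 × 2 × 4 × 10.4976 / δ² = 335.92 / δ²

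| Assumed δ | Total N before dropout |
|---|---|
| 0.8 | 524.9 |
| 0.9 | 414.7 |
| 1.0 | 335.9 |

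An assumed difference of 0.9 matches 415. The stated size is thus consistent with a two-arm comparison, although this does not prove that it was derived in that way. The sample size and Section 3.5 both fit a two-group trial, while Section 3.3 creates no groups.

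**Order of events.** Section 2 says: "The nationally representative sample will be evaluated at baseline using self-assessment tools and clinical examination". In Table 1 the first clinical assessment stands at T1, after Allocation at 0, and none stands in the enrolment column. Any fix that wants the baseline examination before allocation has to change this table.

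**The case against.** The strongest reply has three parts.

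*Allocation is planned as its own step.* Table 1 shows it after eligibility and consent, and the hidden Figure 1 is captioned as the RCT flowchart. It may show two arms and a random step between them. This stands as far as it goes: a reader might infer from Section 3.3 that the trial is in fact not randomised, and the documents do not support that. They support only that the written procedure contains no random assignment. The reply does not rescue the text of Section 3.3, which labels site selection as the allocation sequence.

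*The every-child wording may describe the intervention's content.* It could mean every child in an intervention nursery, and Section 3.5 presupposes a comparator. That is a fair reading. A reader might infer that all children are treated, but the text does not establish this. It is ambiguous, and it must be reconciled with the planned comparison.

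*Convenient choice of county is not a route to an arm.* This stands in full. A reader might infer from step 1 that convenience decides who gets the intervention. Nothing in the article links county choice to intervention status, and a trial in conveniently chosen sites keeps its internal validity if arms are randomised afterwards. What undermines the comparison is the missing assignment step, not the order of counties.

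**Conclusion.** The point holds as a fault in the written procedure. Section 3.3 offers sampling steps as the allocation sequence, and following them yields no randomised groups. On that procedure the Section 3.5 between-group analyses and the Section 1.1 hypothesis test cannot be regarded as a randomised comparison. This should be corrected before any allocation takes place.

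The effect is on validity and has no numerical size. A reader might try to turn the design effect into a between-kindergarten SD and quote a bias relative to a difference of 0.9. That would need an assumed shift between groups for which the article gives no basis, and the 0.9 is itself back-solved.

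The conclusion rests on the visible text, with Figure 1 unseen. Whether convenient county choice and the absence of small cities from the sampled localities fit the claim of national representativeness is a separate question of external validity. It does not bear on this conclusion.

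**What to change.** 1. In Section 3.3, relabel the county ordering, the availability check, the Excel selection and the e-mails as sampling and recruitment of sites.
2. Add a separate allocation step after kindergarten agreement and parental consent, and state the arms (including what the control group receives), the unit and the ratio. One workable form is to randomise kindergartens as clusters within locality type, from a computer-generated list held by someone not involved in recruiting sites.
3. In Table 1, place the baseline examination before Allocation where feasible.
4. Reconcile the every-child wording in Sections 3 and 3.1 with the comparison group in Section 3.5.
5. If allocation has already taken place, report how it was done, and drop the RCT label if it was not random.

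**Cost.** A protocol amendment and a changed timeline. Because sites are recruited county by county, allocation must be sequential or in batches, and batching makes early sites wait. If kindergartens are the unit, they are few: the Study Setting subsection lists 4 + 2 × 2 + 4 × 1 = 12 data collection kindergartens, although Section 3.2 allows more in rural areas. Stratification should therefore be kept simple.

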### 3.4. Data Collection and Management

Data will be collected in order to evaluate the daily tooth-brushing program and the number and attendance of children performing daily tooth brushing, and the daily tooth-brushing activities will be monitored. The number of school days, the fact that on Saturdays and Sundays children will not be present at school, the timepoint of the daily brushing (after the first meal or after lunch), and the hypothesis of morning brushing at home will be considered as variables for data analysis.

To assess oral health promotion activities, self-administered questionnaires (using the Likkert scale) before and after the activities will be used to test the ability of hygienists to pass the information to nursery staff, parents, and children developing a framework to assist in the application of capacity-building principles to public health.

Plans for the assessment and collection of outcome, baseline, and other trial data, including any related processes to promote data quality (e.g., duplicate measurements, training of assessors) and a description of study instruments (e.g., questionnaires, laboratory tests) along with their reliability and validity, will be drafted. Data collection forms can be obtained from the corresponding author.

Feedback from stakeholders on barriers/facilitators across the processes will be obtained and the behavior of children, parents, nursery staff, and dental hygienists will be monitored, using quantitative and qualitative methods to assess parents’ attitudes toward the project’s activities and dental hygienists’ and educators’ perceived barriers to delivering the tasks. Quantitative measures will use questionnaires to assess variables. Interviews with parents, educators, and stakeholders will ensure qualitative data to assess different tasks.

### 3.5. Statistical Methods for Primary and Secondary Outcomes

Caries activity levels after implementing the daily tooth-brushing scheme will be evaluated as the primary outcome. The outcomes will offer information regarding the particularities of the clinical investigation for the specific age group and the time necessary for the investigation and intervention. Clinical outcomes will be evaluated by using the caries incidence rate, calculated on each tooth as the unit of analysis and evaluated using a multi-step approach:

The net caries increment for initial, moderate, and extensive caries severity using ICDAS (Δ-initial, Δ-moderate, and Δ-extensive) will be calculated at each follow-up examination.

Events will be defined as a tooth receiving a lesion or as the sum of the Δ-caries changes in status recorded at the baseline examination, at the interim, and at the last examination. The number of events will be appraised by subtracting the number of caries-free teeth at the last examination from those at baseline.

Data analysis will be performed using SPSS version 24 (IBM Corp., Armonk, NY, USA) and the R software (R Core Team 2023). SPSS will be used for initial data cleaning, descriptive summaries, and basic inferential tests. R will be used for advanced modeling, intention-to-treat (ITT) analyses, and reproducible visualizations.

Data will be cleaned and validated prior to analysis. Descriptive statistics will be computed using continuous variables—mean ± SD (if normal), or median [IQR] (if non-normal) and categorical variables—counts and percentages. Baseline comparability between groups will be assessed but not tested for statistical significance (in accordance with CONSORT guidelines) [19]. Primary outcomes will be analyzed using the intention-to-treat (ITT) principle. The choice of statistical test depends on the outcome type. For continuous outcomes, linear regression adjusting for baseline, if available, will be used. Logistic regressions will be performed for binary outcomes and Poisson or negative binomial regression could be used for count data. For the longitudinal data, linear mixed models or generalized estimating equations (GEE) will be used to account for within-subject correlation. To explore relationships between secondary variables, correlation analysis will be performed.

The non-parametric Mann–Whitney U test will be applied to assess the differences across the mean number of events between groups.

The efficacy of the treatment will be assessed following the indication of the CONSORT consensus guidelines including both PP (Per Protocol) and ITT (Intention to Treat) protocols to calculate the reduction in risk ratio (RR) and the related number needed to treat (NNT) value. An event will be defined as the change in status at tooth level, i.e., the development of a new lesion or the progression of an existing lesion to a more severe stage. Cox Proportional Hazards models will be run to assess the factors associated with caries change in status. Estimates will be reported in the hazard ratio (HR) and their respective 95% confidence interval (95%CI). For all the statistical analyses, the statistical significance will be set at α < 0.05.

The extent and pattern of missing data will be explored. If data are missing at random, multiple imputations will be used. Sensitivity analyses will compare complete cases with imputed datasets. A two-sided alpha level of 0.05 will be considered statistically significant. For multiple secondary outcomes, false discovery rate (FDR) or Bonferroni correction may be applied. The results will be presented with appropriate tables and figures, for reproducibility.

A major aim of the monitoring and evaluation is to collect data to inform and support the planned longer-term roll-out of the program. Process evaluation will, therefore, be a major component of the evaluation plan, as well as using statistical methods for analyzing primary and secondary outcomes and the reference to where other details of the statistical analysis plan can be found, if not in the protocol.

An assessment of the costs of managing dental caries will be obtained through the triangulation of information collected from the National Insurance House and cost data sourced online. Given the variation in the provision of subsidized care across Romanian regions and the scarcity of information on public sector health care costs, private treatment costs are used as a proxy to estimate the direct costs of dental caries.

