## 4. Expected Outcomes

The primary outcome of the trial will be the assessment of caries incidence, defined as the change in status according to the ICDAS index within the age groups. In addition, data analysis from the trial will provide information on children’s self-assessment of oral health practices and promote oral health activities for children with a focus on age-appropriate key messages and practical preparation for the implementation of the nursery intervention, which consists of a toothpaste/toothbrush scheme with free daily tooth brushing for every 4–6-year-old child attending the nursery. Depending on the region, by using the County Development Index, differences between regions will be assessed in order to establish the efficacy of the program at the national level.

Secondary outcomes will be the skills gained by dental hygienists to deliver oral health promotion to nursery nurses after specific training, and a comprehensive process of parental information and consent and validation that shapes healthy behaviours throughout life.

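### One stated definition of the caries event sums a change at baseline that cannot exist, leaves the reference visit open, and disagrees with the two other event rules in the same section

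*Protocol article*

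**What the plan says.** Section 4 of the protocol article sets the target: "The primary outcome of the trial will be the assessment of caries incidence, defined as the change in status according to the ICDAS index". Section 3.5 then gives several rules for turning examinations into events.

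- **Increment.** A net caries increment (Δ) for initial, moderate and extensive lesions "will be calculated at each follow-up examination". The visit against which the change is measured is not named.
- **Event, two alternatives.** "Events will be defined as a tooth receiving a lesion or as the sum" opens the sentence. The sum is then specified as "the sum of the Δ-caries changes in status recorded at the baseline examination, at the interim, and at the last examination".
- **Count by subtraction.** The next sentence reads: "The number of events will be appraised by subtracting the number of caries-free teeth at the last examination from those at baseline".
- **Event for the risk ratio and number needed to treat.** A later paragraph, which goes on to the Cox model for change in status, defines the event at tooth level as "the development of a new lesion or the progression of an existing lesion to a more severe stage".

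The Mann–Whitney test in Section 3.5 compares the number of events between groups. Section 2 gives the visit frequency: "During the intervention, evaluations will be performed every 6 months".

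**The concern.** A change needs two examinations, so there is none to record at the first. If a programmer fills the baseline term at all, the only available content is disease already present, which is prevalence and not incidence.

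The remaining terms depend on a reference visit that the section does not state. If each Δ is measured from baseline, a lesion that appears early and persists enters the sum at every later visit that is included, so the count depends on when lesions appear as well as how many there are. If each Δ is measured from the previous visit, the sum collapses to the last status minus the first, the interim visit drops out, and a reversal cancels a new lesion.

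What is at stake is the event count behind the primary comparison. Two analysts following Section 3.5 could derive different counts from the same records. If the choice is left open, it can be made after the results are known.

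**Working it through.** The plan states no figure on this point, so there is nothing to reproduce. The check scores example teeth under each stated rule.

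**Inputs and conventions.** Status S is 0 = sound, 1 = initial, 2 = moderate, at the baseline, interim and last examinations (S0, S1, S2). A rise of one stage counts +1 and a fall −1, because Section 3.5 speaks of a net increment. This coding is mine; the section gives none.

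**Formulas**

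- From-baseline sum: (S1 − S0) + (S2 − S0)
- Visit-to-visit sum: (S1 − S0) + (S2 − S1) = S2 − S0
- Subtraction: 1 if caries-free at baseline, minus 1 if caries-free at the last examination
- Tooth-level event: 1 if a new lesion or a progression is seen at any follow-up
- Baseline term, if scored against a sound tooth: +1 for any tooth with S0 > 0, added to either sum

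| Tooth (S0,S1,S2) | From-baseline sum | Visit-to-visit sum | Subtraction | Tooth-level event | Baseline term would add |
|---|---|---|---|---|---|
| New at interim, persists (0,1,1) | 1+1 = 2 | 1+0 = 1 | 1−0 = 1 | 1 | 0 |
| New at last (0,0,1) | 0+1 = 1 | 0+1 = 1 | 1−0 = 1 | 1 | 0 |
| Present throughout, unchanged (1,1,1) | 0 | 0 | 0−0 = 0 | 0 | 1 |
| Present, progresses once (1,2,2) | 1+1 = 2 | 1+0 = 1 | 0−0 = 0 | 1 | 1 |
| New, then reverses (0,1,0) | 1+0 = 1 | 1−1 = 0 | 1−1 = 0 | 1 | 0 |
| Present, reverses (1,0,0) | −1−1 = −2 | −1+0 = −1 | 0−1 = −1 | 0 | 1 |

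The table shows three things.

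1. Repeat counting occurs only with the from-baseline Δ (2 against 1 for the first tooth). Prevalent disease enters only if the baseline term is scored (third tooth).
2. The tooth that progresses once scores 0, 1 or 2 depending on the rule, before any baseline term.
3. The visit-to-visit sum gives a net change. It agrees with the tooth-level event when nothing reverses, and departs from it when something does (last two rows).

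**Size of the repeat counting, from-baseline reading only.** The sentence names one interim and the last examination. Assume four follow-ups (24 months at 6-month intervals), with the interim at the second of them. A lesion first seen by the interim scores 2, and a later one scores 1.

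- Uniform onset: 0.5×2 + 0.5×1 = 1.5 counts per new lesion.
- Later onset, assumed 10/20/30/40% over the four intervals: 0.3×2 + 0.7×1 = 1.3.
- Two groups with equal incidence and these two onset patterns would differ by 1 − 1.3/1.5 = 13%.

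If all four follow-ups were summed, the weights would be 4, 3, 2 and 1. Uniform onset then gives (4+3+2+1)/4 = 2.5, and the later pattern gives 0.4+0.6+0.6+0.4 = 2.0, a 20% difference. The sentence does not name four visits, so these are upper illustrations.

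**The case against.** The strongest reply is that the sum is not the trial's event count. It is one of two alternatives joined by a single word, and the sentence after it obtains the number of events by subtracting caries-free teeth. That subtraction counts no persisting lesion twice and adds no baseline disease. The Mann–Whitney test refers to the number of events, which is the phrase used for the subtraction. The three examinations can also be read as the points between which change is measured. The reference visit is a derivation detail that an article may leave to an analysis plan.

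Much of this stands. A reader might infer that the primary comparison is bound to be inflated 2.5-fold, to show a spurious 20% difference, or to be diluted by baseline disease. The documents do not support that. Repeat counting needs a reference visit that the text does not name, and the larger figures sum four visits where the sentence names two. Any dilution figure would need assumed increments. It would also have to use the survey dmft of 6-year-olds in Section 5 as baseline disease, although that index includes missing and filled teeth and is not an ICDAS change in children aged 4 to 6.

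The reply does not remove the defect. The subtraction is not a way of calculating the sum just defined: it ignores the interim visit and gives 0 for a progressing tooth, which the section's later definition counts as an event. The baseline term and the disagreement between the rules are stated text, not omitted detail.

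**Conclusion.** The point holds for one of the stated event definitions. As written, the sum cannot stand, because it includes a change at an examination where Section 3.5 itself calculates none. Its value otherwise depends on an unnamed reference visit, and it agrees with neither the subtraction nor the tooth-level event in all cases. The clearest measure is the tooth that progresses once: 0 by subtraction, 1 by visit-to-visit sum or tooth-level event, 2 by from-baseline sum. That result needs only the stage coding above.

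The 1.5-fold inflation and the 13% difference are illustrations. They hold only for a from-baseline Δ, a midpoint interim visit and the assumed onset patterns. It is not established that the trial will count lesions repeatedly or add prevalent disease. What is established is that the rules given for the primary event count yield different results on the same records. This should be corrected before any comparison by group.

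**What to change.** Change Section 3.5, and any analysis plan that follows it, as follows.

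1. Remove the baseline examination from the sum.
2. Define Δ as the change in each tooth since the immediately preceding examination.
3. Count each new lesion, or each move to a more severe stage, once, at the first follow-up examination where it is seen. The child's count is the total over all follow-up examinations. This matches the tooth-level event already used for the risk ratio and number needed to treat.
4. State that this count is the number of events in the between-group test. Either delete the caries-free subtraction or keep it as a separately named net measure, saying that reversals cancel new lesions in it and that progression does not register.
5. Use baseline caries status as a covariate in the regression models. The Mann–Whitney test cannot adjust for it.

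The cost is a few sentences and the derivation program. The scheduled examinations already supply the data.
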